### Participants

After the study protocol is publicized through institutional media such as videos, website, and emails, interested individuals will be selected using the SRQ-20. Those scoring 7 points or higher and meeting other eligibility criteria will be invited via email by the researcher as part of a care initiative aimed at learning and practicing evidence-based skills to develop autonomy and self-efficacy in promoting psychological well-being. During this invitation, participants will receive explanations about how the study will work, and those who agree to participate will sign the informed consent form. After completing the self-assessment questionnaires, the first thirty participants will proceed to phase 1 of the study. Upon completion of phase 1, other ninety participants scoring 7 or higher on the SRQ-20 and meeting other eligibility criteria will proceed to phase 2 of the study, being randomized into one of the two arms (M-TBCT or waitlist for treatment).

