### Results

In Phase 1, encompassing a pilot study, the acceptability of M-TBCT will assess participants’ perceptions regarding satisfaction with the M-TBCT protocol through a self-report questionnaire. The feasibility of M-TBCT will be verified by recruitment rates (>80 %), session attendance (>60 %), and sample retention at the end of the study (>60 %).

In Phase 2, involving the efficacy of M-TBCT, the primary outcome will be assessed by the increase in well-being, measured through WHO-5. Secondary outcomes include a reduction in depression symptoms (PHQ-9), anxiety (GAD-7), cognitive distortions (CD-QUEST) and an increase in self-care capacity (ASAS-R). All scales will be administered in both groups (M-TBCT and waitlist) before the intervention (baseline assessment), at the end of the 8 sessions (final assessment), and at the 6-month follow-up. Table 2 illustrates the session and assessment flow throughout the study period.

**Table 2 tbl0002:** Session and assessment flow throughout the study period.

Study period				
	Enrollment	Allocation	Post-intervention	Follow-up
**Point in time**	Screening	Baseline	8 weeks	6 months

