Acceptability assesses participants’ perceptions of satisfaction with the M-TBCT protocol. All participants who complete the eight sessions of the program will be invited to complete a self-report questionnaire asynchronously, individually, and online within one week after the intervention. The questionnaire consists of two parts. The first part contains 6 items scored from 0 to 4, where 0 = completely dissatisfied and 4 = completely satisfied, covering the following topics: (1) motivation to participate in the program; (2) therapist's competence; (3) online modality of the intervention; (4) session duration; (5) weekly interval between sessions; (6) quantity and quality of services offered (intervention and support materials); (7) utility of the program in resolving and/or dealing with problems; (8) if the program met expectations; (9) if they would recommend the intervention to others; (10) if they would use the program again; (11) if the program contributed to adhering to what was learned, and (12) overall satisfaction with the program. This part of the questionnaire was adapted from Loucks et al. [30] and Martínez-Sanchis et al. [31]. According to these authors, an intervention is considered well-received when most assessed aspects are recognized by participants as appropriate.

The second part of the questionnaire was adapted from Soler et al. [23], including structured questions about the acceptability and feasibility of the M-TBCT protocol, aiming to cover: (1) the respondent's understanding of well-being and self-care; (2) verifying if and how the protocol contributed to the promotion of well-being and self-care in their daily lives; (3) identifying the practices learned in the protocol that most contributed to the promotion of well-being and self-care in daily life; (4) verifying if there were any challenges that the participant encountered in adhering to the protocol sessions and including practices in daily life; and (5) identifying if there were any practices learned in the protocol that were easier to include in daily life.

According to the literature, the feasibility of an intervention requires meeting at least three of the following indicators: (1) recruitment rate greater than 80 % of the sample size; (2) retention rate equal to or greater than 60 % measured by participation in the final follow-up assessment; (3) attendance rate equal to or greater than 60 % of the total sessions; and (4) intervention evaluation [32].

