### Sample size (Phases 1 and 2)

The sample will consist of magistrates and public servants from the judiciary who score a minimum of 7 points on the recruitment instrument (SRQ-20), which is available for online completion throughout the regional jurisdiction via an electronic platform integrated into TRT5’s intranet.

The sample size for Phase 1 of the study was determined with Soler et al. [23] as a reference, considering a minimum of 30 participants. For Phase 2, the study primarily referred to a meta-analysis conducted by Khoury et al. [39], which assessed the effectiveness of 8-week mindfulness-based interventions in healthy individuals and found an average dropout rate of 10 %.

To establish statistical significance, a sample size of 72 individuals was estimated using G*Power 3.1.9.2, based on a one-tailed *t*-test for independent samples with α=0.05, β=0.20, and Cohen's *d* = 0.6. Considering an approximate dropout rate of 25 %, which is higher than that found in similar studies, an estimated recruitment of approximately 90 eligible individuals for the intervention and control groups is anticipated.

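### Phase 1 feasibility is defined by two different rules, one of which lets H1 be met with retention failing, and retention is tied to an assessment that Phase 1 does not schedule

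*Protocol article*

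**What the plan says.** The Results section of the protocol article introduces the Phase 1 criteria with "The feasibility of M-TBCT will be verified by recruitment rates". In full they are "recruitment rates (>80 %), session attendance (>60 %), and sample retention at the end of the study (>60" %. The three are joined by a plain conjunction, with strict inequalities and no allowance for missing one.

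The Instruments section, under acceptability and feasibility (phase 1), says with reference to the literature that "the feasibility of an intervention requires meeting at least three of the following indicators". Four indicators follow:

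- recruitment above 80% of the sample size;
- "retention rate equal to or greater than 60 % measured by participation in the final follow-up assessment";
- attendance at 60% or more of the sessions;
- "intervention evaluation", with no cut-off beside it.

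The same section invites only participants who complete all eight sessions to fill in the acceptability questionnaire. Table 2 shows that questionnaire, at the post-intervention visit, as the only Phase 1 assessment. All 6-month entries in the table are for Phase 2 scales.

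The sample size section sets Phase 1 by "considering a minimum of 30 participants". For Phase 2 it needs 72 evaluable participants (one-tailed t-test, α = 0.05, β = 0.20, d = 0.6). The inflation sentence begins "Considering an approximate dropout rate of" and gives 25%, with about 90 to be recruited. Under Participants, "the first thirty participants will proceed to phase 1 of the study", and Phase 2 follows once Phase 1 is completed.

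**The concern.** Feasibility is half of H1, so it needs one rule fixed in advance. With two rules of different strictness, the same pilot data can support or reject H1, and the choice could be made after the data are seen. The looser rule is looser where it matters most: it allows retention to fail outright.

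The retention indicator also lacks a usable measurement in Phase 1. If the only Phase 1 questionnaire is taken as the final assessment, then only people who attended all eight sessions can be counted as retained, and retention becomes full completion under another name.

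Finally, the floor of 60% is not linked to the loss that Phase 2 is planned to absorb. A pilot could be reported as feasible at a retention level that Phase 2 was not sized for, with nothing in the text prompting anyone to notice.

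**Working it through.** **1. The two rules side by side**

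| Element | Results | Instruments |
|---|---|---|
| Criteria | three, together | any three of four |
| Recruitment | > 80% | > 80% |
| Attendance | > 60% | ≥ 60% |
| Retention | > 60% | ≥ 60% |
| Retention measured at | end of the study | final follow-up assessment |
| Intervention evaluation | not a feasibility criterion | fourth indicator, no cut-off |

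**2. Where they give opposite answers (30 participants)**

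- Retention of exactly 18/30 = 60% fails the strict inequality and meets the other. The lowest passing count is 19 under Results and 18 under Instruments.
- Retention of 12/30 = 40%, other indicators met, fails under Results and passes under Instruments.
- The second case is arithmetically possible. Suppose 12 people attend all 8 sessions and 18 attend 3 each. Attendance pooled over sessions (an assumption, as the article does not say how it is computed) is (12 × 8 + 18 × 3)/(30 × 8) = 150/240 = 62.5%, which meets the attendance criterion.

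**3. The plan's own Phase 2 figure**

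Power uses the non-central t distribution with n₁ + n₂ − 2 degrees of freedom and non-centrality d·√(n₁n₂/(n₁ + n₂)). With d = 0.6, one-tailed α = 0.05 and 36 per arm, the non-centrality is 0.6 × √18 = 2.546 and power is 0.809. The 72 therefore reproduces. The 90 reproduces as 72 × 1.25; it covers 1 − 72/90 = 20% loss. That is a separate matter and is not relied on here.

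**4. What the 60% floor would mean for Phase 2 (90 randomised, 45 per arm)**

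| Loss assumed | Completers | One-tailed power, d = 0.6 |
|---|---|---|
| 20% in both arms | 36 + 36 | 0.81 |
| 25% in both arms | 67.5 in total | 0.79 |
| 40% M-TBCT, 25% waitlist | 27 + 34 | 0.74 |
| 40% M-TBCT, 20% waitlist | 27 + 36 | 0.75 |
| 40% in both arms | 27 + 27 = 54 | 0.70 |

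**5. What 30 participants can tell**

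- If true retention is 70%, below the 75% that Phase 2 assumes, P(at least 18 of 30) = 0.92 and P(at least 19 of 30) = 0.84. The 60% floor will seldom flag such a shortfall.
- If true retention is 75%, P(at least 23 of 30) = 0.51 and P(at least 24 of 30) = 0.35. A hard pass mark at 75% or 80% would often fail a pilot that meets the planning assumption.
- The exact 95% confidence interval for 18/30 runs from 0.41 to 0.77.

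**The case against.** The strongest defence is that the sections can be read together: Results says what this study will do, Instruments reports a general standard from the literature, and meeting all three criteria in Results automatically satisfies at least three of four. That holds in one direction only. Instruments is where the Phase 1 indicators are set out in detail, and nothing says which section governs when retention fails and the other three indicators are met.

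A reader might infer several stronger points that the documents do not support:

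- **That the rule is a gate to Phase 2.** Participants says only that Phase 2 follows completion of Phase 1. The Instruments rule concerns feasibility of the intervention. No go/no-go is stated.
- **That acceptability has no criterion at all.** Instruments says an intervention is well received when most assessed aspects are judged appropriate. This is loose and not linked to the fourth indicator, but it exists.
- **That the recruitment criterion is automatic because the first thirty are taken.** The article does not give the size of the eligible pool, so this cannot be shown.
- **That Phase 2 power would fall from 80% to 58%.** The 58% is the two-sided figure with 27 per arm. Two-sided power is already 0.71 with all 72 retained, so part of that drop belongs to the choice of a one-tailed test. The pilot has no waitlist arm, so it says nothing direct about loss there.

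It is also fair that a minimum acceptable level is not an expected rate, so 60% and 25% do not strictly contradict each other. And intention-to-treat analysis with mixed models may recover some information from incomplete participants, although the sample size itself rests on a t-test with 72 evaluable.

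**Conclusion.** The contradiction stands. Two sections give different rules for the same Phase 1 decision, and a pilot with poor retention fails H1 under one and can pass under the other. The difference between strict and non-strict inequality matters only at exactly 60%; the difference between all three and any three of four matters at every retention level below that. The retention time point is also unresolved, because Table 2 schedules no follow-up for Phase 1 and the only questionnaire reaches completers alone.

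The mismatch with Phase 2 is real but moderate: one-tailed power of about 0.70 if both arms lose 40%, and about 0.74 if only the M-TBCT arm does and the waitlist loses 25%. These figures assume d = 0.6, 90 randomised 1:1 and an analysis of completers by t-test. The mismatch calls for an explicit comparison of pilot retention with the planning assumption. It does not show that the pilot can license an unsupportable trial, because the article does not make feasibility a formal condition for Phase 2.

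**What to change.** - State one rule in both Results and Instruments: recruitment, attendance and retention must all be met, with one inequality sign throughout.
- Report acceptability separately, against the existing criterion that most assessed aspects are judged appropriate.
- Define Phase 1 retention as completing the 8-week assessment among all who started. Send that assessment to all of them, not only to those who attended eight sessions; otherwise the definition collapses into full completion. Align Table 2 with this.
- Before Phase 2 starts, compare the pilot's observed retention and its confidence interval with the 25% dropout allowance, and say what will be reviewed if it falls short. With 30 participants the interval is wide, so this informs the sample size without deciding it.
- A hard pass mark of 75% (23 of 30) or 80% (24 of 30) is optional. If one is adopted, state that it would pass a pilot with true retention of 75% only 51% or 35% of the time.

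The cost is mainly wording, plus sending one questionnaire to participants who stopped early. Requiring all three criteria makes the pilot harder to pass than under the Instruments rule.

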### Data handling

All study-related information will be stored in secure folders with limited access. Paper-based data collection forms will contain only participant numbers to maintain confidentiality and will be stored in a locked cabinet in an area with limited access. Electronic data files will be password protected. The list linking participant numbers and personal information will be stored in a separate password-protected file. Access will be restricted to the research team or designated personnel for 5 years after inclusion. The study has low negligibility risks; therefore, no data monitoring committee will be assigned. Only the first author and lead researchers, or persons assigned by them, will have access to the final dataset. The authors of the final trial report will make substantial contributions to the design, conduct, interpretation, and reporting of the trial. The study findings will be disseminated through publications and scientific presentations, preserving participant confidentiality. Participants and the data-collecting institution will receive copies of the study results.

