## Description of protocol

### Study design

This study consists of two phases. The first is a pilot study to develop the M-TBCT protocol, assessing its suitability and practicality within the judicial context. The second phase is an efficacy trial using a single-blind design with two groups: an M-TBCT intervention group and a waitlist control group. Inspired by Soler et al. [23], the first phase will involve a sample of 30 participants, divided into three blocks of 10, each receiving M-TBCT in eight weekly one-hour sessions. Participant feedback via a self-report questionnaire will guide protocol refinement.

The second phase, an efficacy trial, will have 90 participants randomly assigned to either the intervention or waitlist group, each receiving the same M-TBCT regimen. The M-TBCT protocol will be administered individually on a weekly basis, with each session lasting 1 h and totaling 8 online sessions.

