### Hypotheses

Based on prior research, we hypothesize:

Hypothesis 1 (H1)M-TBCT will demonstrate acceptance and feasibility among judges and public servants in the judiciary.

Hypothesis 2 (H2)M-TBCT will significantly improve psychological well-being, self-care, and reduce anxiety, depression and cognitive distortions compared to the control group.

Hypothesis 3 (H3)The benefits of M-TBCT will be maintained at the six-month follow-up.

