### Therapist

Both studies anticipate the participation of the psychologist and researcher in this study. She is currently the only professional with completed training in both mindfulness strategies through the Mindfulness-Based Health Promotion (MBHP) protocol from the Open Mind Center at the Federal University of São Paulo and in Trial-Based Cognitive Therapy, as developed by [name] [13].

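### Nothing in the plan keeps the Phase 1 satisfaction ratings, which include a rating of the sole therapist, from that therapist, so acceptability is at risk of upward social-desirability bias

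*Protocol article*

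**What the plan says.** All references are to the protocol article.

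- **Hypotheses.** H1 reads "M-TBCT will demonstrate acceptance and feasibility among judges and public servants in the judiciary".
- **Instruments, acceptability and feasibility.** "All participants who complete the eight sessions of the program will be invited to complete a self-report questionnaire asynchronously, individually, and online", within one week of the intervention. The first part is scored 0 to 4. It is described as having 6 items but lists 12 topics, the second of which is "therapist's competence". The criterion is that "an intervention is considered well-received when most assessed aspects are recognized by participants as appropriate"; no numerical cutoff is given. Feasibility requires at least three of four indicators: recruitment, retention, attendance and an evaluation of the intervention.
- **Study design.** Phase 1 has 30 participants in three blocks of 10, and "Participant feedback via a self-report questionnaire will guide protocol refinement".
- **Therapist.** "Both studies anticipate the participation of the psychologist and researcher in this study". On training: "She is currently the only professional with completed training in both mindfulness strategies". The Phase 2 randomization sections describe the psychologist as a lead researcher as well.
- **Data handling.** The section opens by covering all study-related information and then says: "The list linking participant numbers and personal information will be stored in a separate password-protected file. Access will be restricted to the research team". Persons whom the team designates may also be given access. Lead researchers may also use the final dataset.
- **Limitations, item 3.** Social desirability is acknowledged for the self-report measures of well-being and symptoms. The satisfaction questionnaire is not mentioned.

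**The concern.** Coded records with a separately protected key are ordinary practice, and the Data handling section is not wrong in itself. The difficulty appears when it is read with the Therapist and Instruments sections. The person being rated belongs to the group that may open the key, she delivers every session one to one, and the rating follows within a week. Respondents who think their therapist can read their answers tend to soften criticism.

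Three things depend on these answers:

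- the acceptability half of H1;
- one of the four feasibility indicators, which can decide the result if one of the three count-based indicators fails;
- the refinement of M-TBCT between blocks and before Phase 2, where the complaints most worth hearing are the ones most likely to be held back.

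**Working it through.** The plan states no figure for this point, so there is nothing to reproduce. The check has two parts.

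**1. The sections side by side**

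| Question | What the article states | Section |
|---|---|---|
| Who is rated? | The therapist, as one topic of the satisfaction form | Instruments |
| How many therapists? | One, the only person trained in both components | Therapist |
| Is the therapist in the research team? | Yes: study researcher, and lead researcher as worded for Phase 2 | Therapist; Randomization (Phase 2) |
| Who may open the linking list? | Research team or designated personnel; the therapist is not excluded | Data handling |
| Is the form anonymous or independently collected? | Not stated | – |
| Does the form carry a number or name? | Not stated; the sentence on participant numbers concerns paper forms, and this form is online | Data handling; Instruments |
| Is the bias acknowledged for this form? | No | Limitations, item 3 |

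The general access rule therefore admits the person being rated, and no specific rule takes the questionnaire out of it. That this online form is linkable is an inference from the general rule.

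**2. How far a shift could move the result**

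The documents give no expected ratings, no standard deviation, no cutoff and no comparison of anonymous with identified answers. The size of the bias cannot be computed. As an assumption only, let the inflation of an affected item be 0.25 to 1.0 point on the 0–4 scale. The change in the mean over *k* items when one item is affected is shift ÷ *k*:

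- only the competence item, *k* = 12: 0.25/12 = 0.02 to 1.0/12 = 0.08;
- only the competence item, *k* = 6: 0.25/6 = 0.04 to 1.0/6 = 0.17;
- every item affected: the full 0.25 to 1.0.

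If most aspects is read as a simple majority (also an assumption), the form passes with 7 of 12 or 4 of 6 items. The competence item alone then changes the conclusion only if the other items leave the count exactly one short. A shift across all items could change it more readily.

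A per-item illustration shows how much depends on the starting point. Assume an item passes when more than half of 30 respondents rate it favourably, so P(X ≥ 16) with X ~ Binomial(30, p):

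| Favourable share p | P(item passes) |
|---|---|
| 0.45 | 0.231 |
| 0.55 | 0.645 |
| 0.60 | 0.825 |
| 0.80 | 0.9998 |

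A true share of 0.45 reported as 0.60 would move the pass probability from 0.231 to 0.825. A true share of 0.80 leaves almost nothing to move. The rule and the shares are assumed, and 30 respondents presumes that nobody drops out, so the table says nothing about the likely size in this trial.

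**The case against.** The strongest reply is that this rests on silence. A journal article commonly leaves form settings to the full protocol, and the consent material is not shown. The specifications table promises confidentiality, and the Participants section says the study is explained before consent. What respondents believe about who reads their answers is unknown, and the bias depends on that belief.

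Much of this stands. A reader might infer that the ratings are definitely held under a participant number, that the therapist will look at them, or that the H1 result is biased upward. The documents support none of these; they support a risk. A reader might also take the swing from 0.231 to 0.825 as its size, but that needs a per-item cutoff the plan does not contain and a true share placed just below it.

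The reply does not remove the point. The article does describe access to study data, and the rule it gives admits the person being rated. A promise of confidentiality does not separate the therapist from the team that keeps it.

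It is also fair that recruitment, retention and attendance are counts, that feasibility can pass on those three alone, that Phase 1 is mainly descriptive, and that Phase 2 does not wait on an acceptability threshold. This limits the exposure to the parts named above.

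Finally, full anonymity may have a cost. The Statistical methods section plans an analysis of characteristics that predict adherence and does not define adherence as attendance. The questionnaire itself asks about adhering to what was learned and about obstacles to adherence, so that analysis may need a link to the individual.

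**Conclusion.** The point holds as a risk. As written, the plan leaves the sole therapist inside the group with access to coded data and the key, and nothing keeps the Phase 1 satisfaction questionnaire from her. The satisfaction part of H1, the intervention-evaluation indicator and the refinement feedback are at risk of upward social-desirability bias, and the stated limitation does not cover it. The size cannot be derived from the documents.

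The conclusion rests on two assumptions: that the general access rule applies to this online form, and that respondents may believe the therapist can see their answers.

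Inviting only those who complete all eight sessions is a separate source of upward selection. It is not part of this point, and the change below would not remove it.

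**What to change.** State the following in the acceptability part of Instruments and in Data handling, before any Phase 1 rating is collected, because anonymity cannot be restored afterwards:

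1. The questionnaire is collected by one of two routes. Either it carries no name or participant number, or, if the planned adherence analysis needs a link, an existing lead researcher other than the therapist receives the responses and holds the key. The Study settings section shows that other lead researchers exist.
2. By either route, the therapist receives only item totals and pooled comments, and only after each block of 10 has closed.
3. The invitation to the questionnaire tells participants this.
4. Limitation 3 is extended to the satisfaction questionnaire.

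The cost is protocol wording, a form setting and a little of one lead researcher's time. The first route prevents joining ratings to individual characteristics; the key-holder route avoids that loss and is the safer choice while the adherence analysis is undefined.
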